# Targeting hippocampal hyperactivity with real-time fMRI neurofeedback: protocol of a single-blind randomized controlled trial in mild cognitive impairment

**DOI:** 10.1186/s12888-021-03091-8

**Published:** 2021-02-09

**Keywords:** Hippocampal hyperactivity, Real-time fMRI, Neurofeedback, Pattern separation, Episodic memory

## Abstract

**Background:**

Several fMRI studies found hyperactivity in the hippocampus during pattern separation tasks in patients with Mild Cognitive Impairment (MCI; a prodromal stage of Alzheimer’s disease). This was associated with memory deficits, subsequent cognitive decline, and faster clinical progression. A reduction of hippocampal hyperactivity with an antiepileptic drug improved memory performance. Pharmacological interventions, however, entail the risk of side effects. An alternative approach may be real-time fMRI neurofeedback, during which individuals learn to control region-specific brain activity. In the current project we aim to test the potential of neurofeedback to reduce hippocampal hyperactivity and thereby improve memory performance.

**Methods:**

In a single-blind parallel-group study, we will randomize *n* = 84 individuals (*n* = 42 patients with MCI, *n* = 42 healthy elderly volunteers) to one of two groups receiving feedback from either the hippocampus or a functionally independent region. Percent signal change of the hemodynamic response within the respective target region will be displayed to the participant with a thermometer icon. We hypothesize that only feedback from the hippocampus will decrease hippocampal hyperactivity during pattern separation and thereby improve memory performance.

**Discussion:**

Results of this study will reveal whether real-time fMRI neurofeedback is able to reduce hippocampal hyperactivity and thereby improve memory performance. In addition, the results of this study may identify predictors of successful neurofeedback as well as the most successful regulation strategies.

**Trial registration:**

The study has been registered with clinicaltrials.gov on the 16th of July 2019 (trial identifier: NCT04020744).

## Background

Dementia due to Alzheimer’s disease (AD) is a neurodegenerative disorder associated with cognitive and functional decline. The underlying pathological process begins at least a decade before any clinical symptoms [1] and is characterized by neuronal cell death, extracellular deposits of amyloid-ß (Aβ) and intracellular formation of fibrillary aggregates of abnormally phosphorylated tau [2]. Activity in the hippocampus, as measured by functional magnetic resonance imaging (fMRI), is among the key emerging neuroimaging markers that allow an improved AD risk prediction [3]. In AD, hippocampal activity is typically decreased during memory tasks due to hippocampal atrophy. However, several fMRI studies in the prodromal stage of AD (i.e., in Mild Cognitive Impairment, MCI) have found increased hippocampal activity during memory tasks that was associated with memory deficits, subsequent cognitive decline and faster clinical progression [4–6]. Pattern separation, a process thought to critically depend on the hippocampus, has been particularly used as a task to show increased hippocampal activity in patients with MCI [7, 8]. Pharmacological treatment of hyperactivity in patients with MCI, or in mice with increased levels of Aβ, significantly reduced activity in the hippocampus and improved memory performance in pattern separation tasks [7]. Although one may expect that reducing brain activation in a given area will lead to a drop in performance, there is emerging evidence that hyperactivity in the hippocampus has a negative, rather than a positive, impact on cognition [9]. Thus, reducing excess hippocampal activity may present a promising therapeutic target. Pharmacological interventions, however, are prone to side effects such as headache, diarrhoea, or sleep disturbances. In addition, an elderly population is likely to be on other medication so - apart from the possible side effects - drug interaction may be a problem. An alternative approach may be real-time fMRI neurofeedback. With real-time fMRI neurofeedback, participants train to voluntarily ‘control’ region specific brain activity [10, 11]. The training is accomplished by continuously measuring brain activity in real-time, and providing feedback to the participant about the ongoing activity in the targeted brain area [11].

The current study aims to test whether real-time fMRI neurofeedback is capable of reducing hippocampal hyperactivity in patients with MCI and, in addition, whether the reduction of hyperactivity will be associated with an improvement in memory performance. Comparable to previous studies, we will deploy pattern separation tasks to assess hippocampal activity as well as memory performance (e.g., [7, 8]). As there is evidence for an association between Aβ and hippocampal hyperactivity [9], we will determine Aβ levels in blood. In addition, we will examine variables that may predict neurofeedback success and identify the most successful regulation strategies.

## Methods

### Participants eligibility and recruitment

Eligible participants will be between 60 and 80 years of age, fluent in German, with normal or corrected-to-normal vision. Patients with MCI will be included if their memory performance is below age-, gender-, and education-adjusted norms as assessed with the delayed recall score of a list of words included in the CERAD neuropsychological battery (CERAD [12];). Other cognitive functions may also be below the norm but an impairment in memory performance is mandatory since this subgroup is particularly prone to hippocampal hyperactivity [7]. In addition, they will need to a) report a cognitive complaint, b) show no impairment in activities of daily living, c) show no dementia but d) show signs of neuronal injury (i.e., atrophy in the hippocampus or the medial temporal lobe) according to updated criteria [13]. This will provide intermediate certainty that MCI will develop into AD [13].

Healthy elderly participants will be included if their Montreal Cognitive Assessment (MoCA) score is ≥26 [12] and their Geriatric Depression Score (GDS) is ≤5 [14]. All participants will need to give written informed consent before the study. Exclusion criteria would be major psychiatric, neurological, or medical disorders or a history of epilepsy or severe head injury, current or life-time substance abuse, contra-indications to MRI, or psychoactive medication.

We will recruit healthy elderly volunteers via newspaper advertisements. Patients with MCI due to AD pathology will be recruited from the local memory clinic where they will receive their diagnosis. The study has been approved by the Ethics Committee of the Canton of Bern (2019–00958) and will be conducted in accordance with the declaration of Helsinki. Recruitment will continue until the required number of participants is reached.

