### Screening assessment and group allocation

We will screen participants during a telephone call (and only invite them to participate in the study if deemed eligible). Those who will meet inclusion criteria will be randomly assigned to the experimental group or the control group. The experimental group will downregulate activity in the hippocampus; the control group will downregulate activity in the intraparietal sulcus, a region that plays a key role in spatial attention [15] but not in pattern separation or memory. The participants will not be informed which area they will need to regulate (i.e., from which area they will receive feedback). Thus, we will apply a single-blind, randomized, parallel-group design. Choosing an alternative region in a control group will ensure physiological specificity to ensure that only the regulation of hippocampal activity (and not the regulation of any other brain region) will lead to a reduction of hippocampal hyperactivity and, in consequence, to an improvement in memory performance [16]. Group allocation will be conducted by the Clinical Trials Unit Bern with computer-generated random numbers, stratified for age, gender, and group status (i.e., MCI or healthy volunteers).

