### Statistical analyses

The primary outcome is the change in hippocampal activity as assessed with a pattern separation task during fMRI before and after both neurofeedback sessions. For the determination of intervention effects on hippocampal activity, we will compute repeated measures ANOVA with intervention (experimental vs. control group) and group (healthy volunteers vs. patients with MCI due to AD) as between-subject factors. We will include the genetic variants of ApoE and BDNF as covariates. Next, we are planning to compute regression analyses since we hypothesize that the reduction of hippocampal activity will be associated with memory performance change in the pattern separation task and the VLMT. As exploratory analyses, we will investigate whether any variable predicts successful neurofeedback; we will calculate the association between Aβ levels in blood and hippocampal activity; and we will identify the most successful downregulation strategies. For the prediction of successful neurofeedback, we will apply machine learning methods (e.g., cross-validated non-linear multivariate classification) to obtain the most important features.

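### The ANOVA contrasts MCI with healthy participants but names only ApoE and BDNF as covariates, so its non-randomised diagnosis terms can partly reflect age, gender or education.

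*Protocol article*

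**What the plan says.** All statements are in the Methods of the Protocol article.

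- **Source of participants** (Participants eligibility and recruitment). Healthy group: "We will recruit healthy elderly volunteers via newspaper advertisements". MCI group: "Patients with MCI due to AD pathology will be recruited from the local memory clinic where they will receive their diagnosis".
- **Entry rules** (same section). Healthy group: "Healthy elderly participants will be included if their Montreal Cognitive Assessment (MoCA) score is ≥26 [12] and their Geriatric Depression Score (GDS) is ≤5". MCI group: "Patients with MCI will be included if their memory performance is below age-, gender-, and education-adjusted norms", together with a cognitive complaint, preserved daily activities, no dementia and signs of neuronal injury. The only demographic limit that both groups share is the age window of 60 to 80 years.
- **Randomisation** (Screening assessment and group allocation). Allocation to hippocampal or control-region feedback is "stratified for age, gender, and group status (i.e., MCI or healthy volunteers". Education is not a stratum.
- **Model** (Statistical analyses). The primary outcome is the change in hippocampal activity. The repeated measures ANOVA has intervention and diagnosis as between-subject factors, and on covariates the text says: "We will include the genetic variants of ApoE and BDNF as covariates".

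**The concern.** Intervention is randomised; diagnosis is not. A difference between MCI and healthy participants, in activity or in response to feedback, is a comparison of two samples drawn from different places under different rules. Any variable that differs between the samples and relates to hippocampal activity contributes to that difference unless the design or the model deals with it.

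The article itself treats the relevant variables as important. Age, gender and education enter the norm that defines impaired memory, and age and gender are randomisation strata. ApoE is made a covariate because it seems to influence hippocampal activity, and the same reasoning applies to age. Yet the covariates are named explicitly and none of these three is among them.

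At stake is the reading of the diagnosis factor and of the group by intervention term. A reader will take the first as saying how activity in MCI differs from that in healthy ageing, and the second as saying whether patients respond differently to feedback. Half the sample, 42 of 84, is recruited to make those readings possible.

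**Working it through.** **1. The plan's own figure.** The plan gives no figure for this point. Its one calculation is the sample size: f = 0.25, alpha 0.01, power 0.99, 4 groups, 4 measurements. With correlation rho = 0.5 and epsilon = 1 (assumed, since neither is stated), the noncentrality is f² × N × m / (1 − rho) = 0.0625 × 84 × 4 / 0.5 = 42, with 9 and 240 degrees of freedom. Power is 0.992, so 84 reproduces. This point does not bear on that number.

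**2. What balances what.** Within each diagnosis, participants are randomised to the two feedback arms with age and gender as strata. Group status is also a stratum, so the arms are compared like with like inside MCI and inside healthy. No randomisation acts across diagnoses. Of the steps the article describes, only the shared 20-year age window limits a demographic gap between MCI and healthy participants.

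**3. Bias in the diagnosis main effect.** Let a covariate differ by d SD between the groups and correlate r with the outcome. The spurious difference is r × d in outcome SDs. The documents give neither quantity, so both are assumptions: d from 0.25 to 0.8 and r from 0.1 to 0.4.

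- Smallest: 0.1 × 0.25 = 0.025 SD. Largest: 0.4 × 0.8 = 0.32 SD.
- Standard error with 42 per group: sqrt(2/42) = 0.218 SD.
- z = bias / standard error: 0.025 / 0.218 = 0.115 and 0.32 / 0.218 = 1.466.
- Rejection rate with no true difference: Φ(z − z_crit) + Φ(−z − z_crit), where z_crit is the two-sided critical value.

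| d | r | bias (SD) | nominal 5% | nominal 1% |
|---|---|---|---|---|
| 0.25 | 0.1 | 0.025 | 5.2% | 1.0% |
| 0.5 | 0.3 | 0.15 | 10.6% | 3.0% |
| 0.8 | 0.4 | 0.32 | 31.1% | 13.4% |

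The 1% column is shown because 0.01 is the only alpha the article states, in the sample size section.

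**4. Group by intervention term.** If the covariate only shifts the outcome, it shifts both feedback arms of a diagnosis equally and cancels. If the feedback effect itself changes by s SD per SD of the covariate, the bias is s × d. With 21 per cell the standard error is sqrt(4/21) = 0.436 SD. For s = 0.3 and d = 0.5 the bias is 0.3 × 0.5 = 0.15 SD, z = 0.15 / 0.436 = 0.344, and the rejection rate is 6.4% at nominal 5% and 1.5% at nominal 1%.

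**5. Simulation check.** 21 per cell, d = 0.5, r = 0.3, no true effects, 8,000 repetitions. Mean estimates:

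- diagnosis main effect: 0.15 SD (formula: 0.3 × 0.5 = 0.15)
- randomised feedback contrast: 0.00
- group by intervention, covariate shifts the outcome only: −0.005
- group by intervention, covariate also modifies the feedback effect (s = 0.3): 0.14 SD

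**The case against.** The strongest reply is that the trial's main question is untouched. The hypothesis is that only hippocampal feedback lowers hippocampal activity, the outcome is within-person change, and that comparison is randomised within diagnosis. This stands in full.

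Three further objections also stand, and they limit the point:

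- A reader might infer that the volunteers are unmatched and that the MoCA threshold is applied without demographic correction. The article says neither. It is a condensed account, and the full protocol may say how advert respondents are accepted.
- A reader might infer that the MCI patients will be older and less schooled, so that the results do mix diagnosis with age and education. No imbalance is shown. The idea that a fixed threshold favours younger, better-educated volunteers rests on an assumption about MoCA that the documents do not supply.
- A reader might expect a badly inflated error rate in a baseline comparison of MCI with healthy activity. The Statistical analyses section lists no such test, and any rate depends on assumed gaps and slopes. Nor do the documents say that age or education modifies the response to feedback, which the group by intervention bias requires.

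One objection stands only in part: that covariates are commonly left to the analysis plan. Here the article names the covariates for a model with a non-randomised factor, so the list is open to comment as written.

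**Conclusion.** The point holds in a limited form. As written, the diagnosis main effect is open to confounding by age, gender and education. The group by intervention term is open to it only if age or education changes how people respond to feedback. The conclusion rests on three stated facts: different sources and entry rules, randomisation that balances only the feedback arms, and a covariate list limited to two genotypes.

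The size cannot be derived from the documents. The calculated range runs from negligible to a roughly sixfold error rate (31% against 5%) for the diagnosis effect, and its upper end needs both a large gap and a fairly strong correlation. The group by intervention term is less exposed, because its standard error is twice as large. The hippocampal-versus-control feedback comparison needs no correction on this account. This is an inexpensive improvement to secondary readings of the model and does not threaten the primary aim.

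**What to change.** In Statistical analyses:

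1. Add age and gender, which are already randomisation strata, and years of education to ApoE and BDNF as covariates in the ANOVA. Because the outcome is a change, enter them with their terms by time so that the adjustment reaches the change as well as the level.
2. If a group by intervention result is interpreted, report a sensitivity analysis that adds age by intervention and education by intervention.
3. State that MCI-versus-healthy contrasts are non-randomised and are to be read as such.

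The cost is a few degrees of freedom in the main model and some loss of precision in the sensitivity model, which has only 21 participants per cell. Age and gender are needed for the stratification, and education is needed for the MCI norms; for volunteers it is one extra question if not already recorded.

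Frequency-matching volunteers to the MCI group on age, gender and education during recruitment is an optional addition. It would limit extrapolation in the adjusted model, but it means turning away some respondents and letting healthy recruitment follow MCI recruitment. If the full protocol already provides for matching, one sentence in Participants eligibility and recruitment would make that clear.

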### Screening assessment and group allocation

We will screen participants during a telephone call (and only invite them to participate in the study if deemed eligible). Those who will meet inclusion criteria will be randomly assigned to the experimental group or the control group. The experimental group will downregulate activity in the hippocampus; the control group will downregulate activity in the intraparietal sulcus, a region that plays a key role in spatial attention [15] but not in pattern separation or memory. The participants will not be informed which area they will need to regulate (i.e., from which area they will receive feedback). Thus, we will apply a single-blind, randomized, parallel-group design. Choosing an alternative region in a control group will ensure physiological specificity to ensure that only the regulation of hippocampal activity (and not the regulation of any other brain region) will lead to a reduction of hippocampal hyperactivity and, in consequence, to an improvement in memory performance [16]. Group allocation will be conducted by the Clinical Trials Unit Bern with computer-generated random numbers, stratified for age, gender, and group status (i.e., MCI or healthy volunteers).

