### Sample size calculation

For the determination of sample size, we used G*power [32]. Since no study so far tried to downregulate hippocampal activity, we opted for the detection of at least a small effect (i.e., cohen’s *f* = 0.25). This would require an inclusion of *n* = 84 in total (that is, *n* = 21 in each group) for a repeated measures design with 4 groups and 4 measurements (i.e., baseline, post-intervention, follow-up 1, follow-up 2). We used the following criteria to calculate sample size: ANOVA with repeated measurements and between-within interactions, α err = 0.01, 1-β = 0.99, number of groups = 4, number of measurements = 4.

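### Age and gender stratify the randomisation but are missing from the stated primary model; if they predict change in hippocampal activity, the analysis is mildly conservative and loses some power

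*Protocol article*

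**What the plan says.** Under Screening assessment and group allocation, the protocol article states that the trials unit allocates with "computer-generated random numbers, stratified for age, gender, and group status (i.e., MCI or healthy volunteers". No age bands or block size are given.

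Under Statistical analyses, the outcome is defined as follows: "The primary outcome is the change in hippocampal activity as assessed with a pattern separation task during fMRI before and after both neurofeedback sessions". The model is a "repeated measures ANOVA with intervention (experimental vs. control group) and group (healthy volunteers vs. patients with MCI due to AD) as between-subject factors", followed by: "We will include the genetic variants of ApoE and BDNF as covariates". Age and gender are not named.

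A test level appears only under Sample size calculation: "ANOVA with repeated measurements and between-within interactions, α err = 0.01, 1-β = 0.99, number of groups = 4, number of measurements = 4".

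**The concern.** Stratified allocation makes the arms alike on the stratification factors, so part of the chance variation in the treatment comparison disappears. A model without those factors does not register this. Whatever variance they explain stays in the residual, and the standard error is computed as if the arms could still differ on them. The result is a test that rejects less often than its nominal level and has less power than the design could give.

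Here the analysis section names its factors and covariates. It takes in two genotypes that did not constrain allocation and leaves out two variables that did. Because the list is explicit, this is a mismatch between stated design and stated analysis, not a detail left to a fuller document. What is at stake is efficiency in a trial of 84 participants. Validity is not in question.

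**Working it through.** **1. The plan's own figure.** Inputs from Sample size calculation: f = 0.25, alpha 0.01, power 0.99, 4 groups, 4 measurements. Assumed, because not stated: correlation between measurements rho = 0.5 and sphericity epsilon = 1. For the within-between interaction,

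lambda = f² × N × m / (1 − rho) = 0.0625 × 84 × 4 / 0.5 = 42, with df1 = 3 × 3 = 9 and df2 = (84 − 4) × 3 = 240.

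Power at 84 is 0.992. The smallest N reaching 0.99 is 82, which becomes 84 for four equal cells, so the stated figure reproduces. With rho of 0, 0.3 or 0.7 the minimum would be 160, 113 or 51. Age and gender play no part in this calculation.

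**2. What the omission can affect.** Write activity as a stable personal level plus a time effect, with the level depending on age and gender. In the post-minus-baseline difference the level cancels. Only an association of age or gender with the *change* remains in the residual of the time-by-intervention contrast. Let R² be the share of the variance in change that age and gender explain. The documents give no value, so it is varied.

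**3. Upper limit.** If the strata balanced the whole age and gender effect perfectly, the standard error would be overstated by the factor 1/√(1 − R²), and the actual two-sided level would be 2 × (1 − Φ(z/√(1 − R²))).

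| R² for change | SE factor | Level at nominal 0.01 | Level at nominal 0.05 |
|---|---|---|---|
| 0 | 1.000 | 0.0100 | 0.050 |
| 0.05 | 1.026 | 0.0082 | 0.044 |
| 0.10 | 1.054 | 0.0066 | 0.039 |
| 0.20 | 1.118 | 0.0040 | 0.028 |

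**4. Realistic allocation.** Perfect balance is not attainable: age must be banded, and blocks in small strata stay incomplete. A simulation of the change score used 84 participants (42 per diagnosis) and assumed eight strata (diagnosis × gender × two age bands) with blocks of 4. The model contained intervention, diagnosis, their interaction, ApoE and BDNF, with or without gender and continuous age. There were 6,000 runs under no effect.

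| R² | Level without age and gender, nominal 0.01 / 0.05 | Level with them | Mean reported SE, without → with (SD units) |
|---|---|---|---|
| 0 | 0.0105 / 0.051 | 0.0107 / 0.052 | 0.2206 → 0.2211 |
| 0.05 | 0.0105 / 0.049 | 0.0102 / 0.053 | 0.2205 → 0.2153 |
| 0.10 | 0.0097 / 0.039 | 0.0113 / 0.049 | 0.2210 → 0.2099 |
| 0.20 | 0.0050 / 0.034 | 0.0112 / 0.049 | 0.2214 → 0.1980 |

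Simulation error at nominal 0.01 is √(0.01 × 0.99 / 6000) = 0.0013. In the unadjusted model the reported SE exceeded the empirical SE by 0.2205/0.2195 − 1 = 0.5%, 0.2210/0.2113 − 1 = 4.6% and 0.2214/0.2012 − 1 = 10.0% for R² of 0.05, 0.10 and 0.20. All three lie below the limits in step 3.

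**5. Power.** Assumed true difference 0.7 SD of change, alpha 0.01, 3,000 runs:

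| R² | Without | With |
|---|---|---|
| 0.05 | 0.69 | 0.71 |
| 0.10 | 0.71 | 0.76 |
| 0.20 | 0.73 | 0.82 |

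**The case against.** The strongest reply is that nothing in the article ties age or gender to change in hippocampal activity. Their relation to atrophy, or to memory norms, concerns level, and level cancels. This stands, and it makes the loss conditional.

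A second reply is that the effect is small even where it exists. This stands for weak associations: up to R² of about 0.05 the loss of level cannot be told from simulation error, and the power gain is about 0.02. It does not stand at R² of 0.20, where the gain is about 0.09.

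A reader might go further and infer that the actual level is known to lie below 0.01, for example 0.008 or 0.007. The documents do not support that. Those values are the perfect-balance limits for R² of 0.05 and 0.10, and with finite blocks the simulated levels were 0.0105 and 0.0097, neither distinguishable from 0.01. If R² is zero, the level is exact. Moreover, 0.01 is stated only for the sample size, and the analysis section sets no test level. Nor are lost precision and a conservative level two separate harms: both follow from one inflated residual variance.

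A reader might also extend the point to the planned regressions of memory change on reduction in hippocampal activity. The exposure there is not randomised, so the argument from stratified allocation does not carry over.

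**Conclusion.** The mismatch is real and can be read directly from the article: three stratification factors, of which one is in the primary model. The consequence is conditional. If age or gender predicts change, the unadjusted analysis is mildly conservative and gives up some power; the treatment estimate is not biased and false positives do not increase. For assumed R² of 0.05, 0.10 and 0.20 the standard error is overstated by at most about 3%, 5% and 12%. The power figures rest further on a 0.7 SD difference, alpha 0.01, two age bands and blocks of 4, none of which the article fixes for the analysis or the allocation, apart from the alpha in its sample size section. The point is an inexpensive improvement and does not threaten the trial's conclusions.

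**What to change.** Add age (continuous) and gender to the primary model alongside diagnosis and the two genotypes, and say how they enter. Main effects alone are not enough: in a repeated-measures ANOVA with complete data they leave the within-subject time-by-intervention test unchanged. Either include age-by-time and gender-by-time terms, or analyse the change score (or post-intervention activity by ANCOVA on baseline) with age and gender as covariates.

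The cost is two parameters in the change contrast: residual degrees of freedom in the change-score model go from 84 − 6 = 78 to 84 − 8 = 76. If age and gender turn out to be irrelevant, the mean standard error moves only from 0.2206 to 0.2211. Both variables must be known in order to randomise, so no data collection is added, and N stays at 84.
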